### Randomisation and blinding

The physical therapy practices of the participating physical therapists will be the unit of randomisation (cluster). Each practice will be randomly assigned to either the intervention or control arm on a 1:1 basis. The allocation sequence will be generated online (with a block size of six) [25] using http://randomization.com by the principal investigator. Participating practices will be randomised in the order that they confirm their participation in the study. The practices will be informed about the group allocation by the principal investigator. Based on the randomisation, physical therapists working in the randomised practices will be able to use all the ‘WORK TO BE DONE’ intervention components (intervention group) or will continue providing regular physical therapy to their patients (control group). Physical therapists and patients cannot be blinded to allocation group.

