### Sample size

The sample size was calculated based on the main outcome measures (11-item NPRS and 11-point PSFS), an expected effect size of 0.7 and a standard deviation of 1.8 [32, 45–47]. On the basis of two-sided testing, significance level of 0.05, power 0.8, accounting for the cluster design effect, assuming an ICC coefficient of 0.05, and 15 clusters per intervention arm, an effective sample size would require 10 patients per cluster (i.e. per physical therapy practice). With respect to the effect of cluster size variation, we added 10% additional clusters (in total 17 clusters per arm) [48]. Allowing for a 25% loss to follow-up, we would need to recruit 13 participants (i.e. patients) per cluster [49]. In total, we need to include 221 patients in each arm (442 in total).

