### Data analyses

Analysis of the two groups will be conducted blinded to the treatment allocation and the data will be analysed according to the intention-to-treat principle. Baseline characteristics of the participants will be presented in means and standard deviations (symmetrically distributed continuous variables), median interquartile ranges (other continuous variables), and counts and percentages (categorical variables), and will be checked for baseline differences between the two groups.

All outcome measurements will be continuous variables and will be presented as means and standard deviations. Normality of the data will be checked and verified using histograms, normal probability plots and Shapiro-Wilk tests. Between-group differences for all outcomes will be analysed using linear regression. If data appears to be not normally distributed, Mann-Whitney U tests or log transformation will be performed.

Each outcome variable will be analysed independently at T1 and at T2 [50] as a dependent variable using the study group as an independent variable, adjusted for the baseline measurement of each outcome measure. Adjustment for confounding will only be applied if the regression coefficient of the intervention variable changes by more than 10% when the potential confounding variable is added to the model. If missing data for an outcome is > 5%, multiple imputation will be conducted. Results will be considered significant if p < 0.05. All analyses will be performed using IBM SPSS Statistics 26 (IBM Corporation).

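### The stated analysis leaves out practice, the unit of randomisation, so at the plan's own ICC a nominal 5% test runs at about 10%

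*Protocol article*

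**What the plan says.** Three sections of the protocol article bear on this.

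- **Randomisation and blinding:** "Each practice will be randomly assigned to either the intervention or control arm on a 1:1 basis". The practice is the cluster.
- **Sample size:** the calculation uses "an expected effect size of 0.7 and a standard deviation of 1.8" and proceeds by "accounting for the cluster design effect, assuming an ICC coefficient of 0.05, and 15 clusters per intervention arm". Clusters are then added for unequal practice sizes, and patients for 25% loss to follow-up.
- **Data analyses:** "Between-group differences for all outcomes will be analysed using linear regression". T1 and T2 are analysed separately, with study group as the independent variable and adjustment for the baseline value. Confounders enter by a 10% change-in-coefficient rule. For non-normal data the fallback is a Mann-Whitney U test or a log transformation. If more than 5% of an outcome is missing, "multiple imputation will be conducted". Significance is p < 0.05.

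The article names no random practice effect, estimating equations, cluster-robust variance or practice-level summary.

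**The concern.** Patients treated in the same practice tend to have correlated outcomes, and the whole practice receives one allocation. A regression that counts each patient as an independent unit overstates the information on the group difference. Its standard errors are too small, its p-values too low and its confidence intervals too narrow.

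The Mann-Whitney test rests on the same independence assumption. A log transformation changes the scale but does nothing about clustering.

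The error goes one way and touches every primary and secondary outcome at both time points. The sample size section recognises the correlation and the analysis section drops it, so the two do not describe the same trial.

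**Working it through.** **Inputs from the Sample size section:** difference 0.7 points, SD 1.8, two-sided alpha 0.05, power 0.80, ICC 0.05, 15 practices per arm with 10 patients each, raised to 17 practices with 13 recruited, 25% loss.

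**1. Reproduce the plan's figure.**
- Independent patients per arm: 2 × [1.8 × (1.960 + 0.842) / 0.7]² = 103.8, so 104.
- Design effect (DE) with 10 per practice: 1 + (10 − 1) × 0.05 = 1.45.
- Needed per arm: 104 × 1.45 = 150.8, against 15 × 10 = 150 in the plan (power 0.799).
- 15 × 1.1 = 16.5, rounded to 17; 17 × 13 = 221 per arm; 2 × 221 = 442.

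The plan's number is reproduced, and it contains the design effect.

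**2. Error rate if practice is ignored.** The naive standard error is the true one divided by √DE, so the actual two-sided error is 2 × [1 − Φ(1.96 / √DE)].

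| Completers per practice | ICC | DE | Naive SE / true SE | Actual error |
|---|---|---|---|---|
| 9.75 (13 × 0.75) | 0.05 | 1.4375 | 0.834 | 0.102 |
| 10 | 0.05 | 1.45 | 0.830 | 0.104 |
| 13 (no loss) | 0.05 | 1.60 | 0.791 | 0.121 |

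In the first row a nominal 95% interval covers 1 − 0.102 = 89.8%.

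**3. Sensitivity (assumed values).**
- ICC remaining after baseline adjustment, 10 per practice: 0.01 gives 0.061, 0.02 gives 0.071, 0.03 gives 0.082, 0.10 gives 0.155.
- Unequal practice sizes, mean 9.75, ICC 0.05, DE = 1 + [(1 + CV²) × 9.75 − 1] × 0.05: CV 0.4 gives DE 1.516 and error 0.111; CV 0.6 gives DE 1.613 and error 0.123.

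**4. Simulation under no effect** (17 practices per arm, 10 patients each, residual ICC 0.05, assumed baseline-outcome correlation 0.5, 20,000 trials). Baseline-adjusted linear regression without practice rejects in 10.3% of trials. A t-test on baseline-adjusted practice means (32 degrees of freedom) rejects in 5.1%. With residual ICC 0.02 the figures are 7.1% and 5.1%. An unadjusted Mann-Whitney test at ICC 0.05 rejects in about 9.5% (5,000 trials).

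**5. Precision.** With 17 × 9.75 = 165.75 completers per arm and SD 1.8, before any gain from baseline adjustment:
- Naive standard error: 1.8 × √(2 / 165.75) = 0.198; half-width 1.96 × 0.198 = 0.39 points.
- With clustering: 0.198 × √1.4375 = 0.237; half-width 1.96 × 0.237 = 0.46 points, or 2.04 × 0.237 = 0.48 with 32 degrees of freedom.
- The interval is therefore 20% wider (√1.4375 = 1.20), or about 25% wider with the small-sample correction (1.20 × 2.04 / 1.96 = 1.25).

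**The case against.** The strongest defence is that the article is a condensed text. It says only linear regression, never that the model has a single level, and the Study setting section states that the study protocol is in a public repository, which is not shown here. That document may name a clustered method. This limits what can be said about how the data will actually be analysed. It does not repair the article, which does not defer: it fixes the model, covariates, fallback test, missing-data trigger, significance level and software, and none of these accounts for practice.

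It is also fair that the doubling depends on an ICC of 0.05 remaining after baseline adjustment. At 0.01 to 0.02 the error is only 6% to 7%.

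A reader might infer more than the text supports:

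- **That separate T1 and T2 models are part of the error.** They are not. Analysis at each time point with baseline adjustment is valid, and the article chooses it deliberately in both the abstract and the analysis section.
- **That the imputation is known to ignore practice.** The article gives no imputation model, and an article commonly leaves that to the fuller plan. No error rate can be attached to it.
- **That the estimated effect is biased or the sample size wrong.** The defect lies in standard errors, intervals and p-values. The number of patients already carries the design effect.

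**Conclusion.** The point holds and should be corrected before the analysis. As published, the analysis contradicts the randomisation and sample size sections, and both the regression and its fallback test are anti-conservative. At the plan's own figures (ICC 0.05, 9.75 to 10 completers per practice, equal practice sizes) standard errors are about 17% too small and the 5% test runs at about 10%. Over an assumed post-adjustment ICC of 0.01 to 0.10 it runs at about 6% to 15%; unequal practice sizes push it up somewhat. The conclusion rests on reading linear regression with the listed terms in its ordinary sense, and on the article alone.

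**What to change.** Replace the regression sentence with wording such as: at T1 and at T2 separately, each outcome is analysed in a linear mixed model with study group and baseline value as fixed effects and a random intercept for practice, using Satterthwaite degrees of freedom because there are only about 34 clusters. A cluster-level analysis of baseline-adjusted practice means is an acceptable alternative.

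Two further changes follow:

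- Replace the Mann-Whitney fallback with a method that respects practice, for example a rank test on practice-level summaries. A log transformation can stay if it is applied within the mixed model.
- If multiple imputation is used, which the planned 25% loss against a 5% trigger makes likely, include practice in the imputation model as a random effect or as indicators.

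Reporting the estimated ICC would be useful. A joint model of T1 and T2 is optional.

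The cost is wording only. The named software fits mixed models and recruitment does not change. Confidence intervals will be about 20% to 25% wider than those from the stated regression, which is essentially the precision for which the trial was sized.

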#### Primary outcomes

##### Limitations in specific work-related activities

The limitations in specific work-related activities in the previous week will be assessed using a patient-specific functional scale (PSFS) [26, 27]. Patients will be asked to identify the most important work-related activity they are unable to perform or are having difficulty with as a result of their musculoskeletal problems. Patients will be asked to rate each activity on an 11-point scale indicating the current level of difficulty associated with each activity. The PSFS is a valid, reliable and responsive outcome measure for patients with MSDs [26, 28–30]. As the minimal clinically important difference (MCID) we will use two points [31–34].

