#### Secondary outcomes

**Limitations in general work-related activities** will be assessed using a single question about the limitations experienced during work in general due to the complaints (11-point scale) [38].

**General pain**. The general level of pain experienced by the patient in the previous week will be assessed using the 11-point numeric pain rating scale (NPRS).

**Quality of life** will be assessed using the 12-item Short-Form Health Survey (SF-12) [39].

**Presenteeism** will be assessed using the Dutch version of the 6-item Stanford Presenteeism Scale (SPS-6) [40].

**Absenteeism** will be measured by asking the patient the number of days they had been out of work due to their complaints during the previous month.

**Estimated risk for future work disability** will be assessed using the Örebro Musculoskeletal Pain Screening Questionnaire (short form) [41].

**Work-related psychosocial risk factors** will be assessed using the blue flags questionnaire [42].

The degree to which health problems interfere with specific aspects of **job performance** and the **productivity impact** of these work limitations will be assessed using the Work Limitations Questionnaire [43].

**Work ability** will be assessed using the Work Ability Index-Single Item Scale (WAS), which is a responsive measure for work participation and highly predictive for future sickness absence [44].

The amount of **attention to work participation** given by the physical therapist, and the **level of satisfaction** of the patient with this attention will be measured using five-point Likert scales.

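### The distribution of the outcome data, judged without a criterion, can replace the baseline-adjusted regression of the primary outcomes with Mann-Whitney or a log transformation

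*Protocol article*

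**What the plan says.** All of this stands in the Data analyses section of the protocol article unless noted.

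- Main analysis: "Between-group differences for all outcomes will be analysed using linear regression", at T1 and T2 separately, "adjusted for the baseline measurement of each outcome measure". Further covariates enter only if they move the treatment coefficient by more than 10%.
- Check: "Normality of the data will be checked and verified using histograms, normal probability plots and Shapiro-Wilk tests". The object of the check is the data; residuals are not mentioned.
- Consequence: "If data appears to be not normally distributed, Mann-Whitney U tests or log transformation will be performed". No threshold is given, no rule selects one option over the other, and no handling of zeros is stated.
- Scope: "All outcome measurements will be continuous variables and will be presented as means and standard deviations". The rule therefore covers both primary outcomes, which are 11-point scales. For the patient-specific functional scale the text reads: "Patients will be asked to rate each activity on an 11-point scale indicating the current level of difficulty associated with each activity". Pain during work uses an 11-point numeric rating scale.
- Under Secondary outcomes, absenteeism is "the number of days they had been out of work due to their complaints during the previous month", and the attention and satisfaction items "will be measured using five-point Likert scales".

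**The concern.** The sentence does more than leave a detail open. It allows the primary analysis to be exchanged for a different one after the data have been seen, on a check that does not bear on the validity of the regression. Linear regression makes no assumption about the marginal distribution of the outcome. If normality is to be looked at, the residuals are the place, and with some 340 patients moderate departures there matter little for a comparison of means.

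The replacements also conflict with the rest of the section. Mann-Whitney takes no baseline covariate and yields no treatment coefficient, so neither the baseline adjustment nor the 10% confounder rule can be applied. It gives no adjusted difference in points, although the trial was sized on one. A log transformation keeps the regression and its covariate, but fails at zero and estimates a ratio. Because the choice can be made separately for each outcome and time point, the two primary outcomes could end up on different scales with different adjustment.

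**Working it through.** **1. The plan's own figure.** From the Sample size section: difference 0.7, SD 1.8, two-sided 0.05, power 0.80, ICC 0.05, 10 patients per practice.

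- Per arm without clustering: 2 × (1.8 × (1.960 + 0.842) / 0.7)² = 103.8, so 104.
- Design effect: 1 + 9 × 0.05 = 1.45. 104 × 1.45 = 150.8, or 15 practices of 10 (power 0.799).
- 15 × 1.1 = 16.5, so 17 practices; 17 × 13 = 221 per arm.

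The figure is reproduced. The 0.7 is thus a difference in scale points (a standardised 0.7 would need only 33 per arm before clustering), and the calculation takes no credit for baseline adjustment. The expected analysis set is 2 × 17 × 10 = 340, or 442 × 0.75 = 332.

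**2. How Shapiro-Wilk behaves on such scores.** Normal scores were simulated, rounded and clipped to 0-10, with assumed means of 2 to 5 and SD 1.8 (documents) or 2.5 (assumed).

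| Tested | N | Rejected at 0.05 |
|---|---|---|
| Raw scores | 332 | 100% |
| Raw scores | 166 (about one arm) | 100% |
| Raw scores | 83 | 66% to 100% |
| Regression residuals (control mean 4, SD 1.8) | 340 | about 9% to 25% |

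The underlying variable was normal throughout, so the raw-score rejections reflect discreteness and the scale limits.

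**3. Zeros under a log.** Assuming zero is the lowest scale point, the share of zeros is Φ((0.5 − mean) / 1.8):

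- mean 5: Φ(−2.50) = 0.6%
- mean 3.5: Φ(−1.67) = 4.8%
- mean 2.5: Φ(−1.11) = 13.3%

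**4. Price of losing baseline adjustment.** Simulated cluster-level analyses with 17 practices of 10 per arm, ICC 0.05, control mean 4, SD 1.8 and effect 0.7:

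| Assumed baseline correlation | Adjusted power | Unadjusted power | Loss |
|---|---|---|---|
| 0.3 | 0.830 | 0.809 | 2 points |
| 0.5 | 0.875 | 0.825 | 5 points |

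**5. Is clustering lost through the switch?** With practices ignored, the analytic type I error is 2 × (1 − Φ(1.960 / √1.45)) = 0.104. Simulated values are 0.095 to 0.101 for Mann-Whitney and 0.104 to 0.122 for the baseline-adjusted regression without a cluster term. The two are alike, and the regression as described names no cluster term.

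**The case against.** The strongest reply is that the trigger is an appearance, formed from histograms and probability plots as well as a test. A statistician who sees a roughly bell-shaped histogram may keep the regression whatever Shapiro-Wilk says. This stands. A reader might infer from the 100% rejection rate that the analysis will almost always switch; the documents do not support that, since the rate belongs to one of three listed tools. It leaves an undefined judgement in charge of the primary analysis, which is itself a defect.

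A reader might also infer that the switch is what discards the clustering and inflates the type I error to about 10%. It is not: the stated regression names no cluster term either and performs no better. That inflation is a separate point, and deleting this sentence alone would not cure it.

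Other points stand in part:

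- Baseline adjustment is lost only under Mann-Whitney, not under a log.
- The power cost is modest, and the unadjusted cluster-level analysis still reaches 0.81 to 0.83.
- Means and SDs will be reported in any case, so a crude difference in points can always be read off; only an adjusted one is lost.
- The analysis is to be masked to allocation. That limits selective choice but does not make the replacement compatible with the planned adjustment.
- The fallback is the section's only provision for skewed or ordinal secondary outcomes, so those need something in its place.

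**Conclusion.** The point holds as a fault in what the section fixes, not as a gap left to an analysis plan. A check on the raw data, without a criterion, may replace the primary regression by one of two analyses with no rule between them. One contradicts the section's own adjustment rules. The other is undefined at zero and changes the effect measure. A needless switch is likely but not certain.

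The measurable harm is moderate: about 2 to 5 points of power if baseline adjustment goes, about 0.6% to 13% of scores unusable under a plain log, and no adjusted estimate on the 0.7-point scale under either option. These sizes rest on assumptions outside the documents: score means, the baseline correlation, and zero as the lowest scale point (the article gives no anchors for the functional scale). SD 1.8 and ICC 0.05 are the protocol's own.

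As a lesser matter, the statement that all outcomes are continuous is wrong for absent days, a count, and for the five-point Likert items.

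**What to change.** 1. Delete the switch for the two primary outcomes. State that each is analysed at T1 and T2 with one linear model, adjusted for its baseline value and accounting for practice, whatever the raw distribution. The practice term has to be written in, because the present text has none to keep.
2. Replace the check on the data by an inspection of residuals, with no change of primary analysis attached to it.
3. Name one alternative in advance, such as a cluster bootstrap or a permutation of practices, as a sensitivity analysis only.
4. Correct the statement that all outcomes are continuous, and name a suitable cluster-aware analysis for the secondary outcomes it misdescribes: for example a negative binomial or hurdle model for absent days, and an ordinal mixed model for the Likert items.

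The cost is a revised paragraph and slightly more programming. No extra patients or data are needed.

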**Methods/design:**

This trial is a two-arm non-blinded cluster randomised controlled trial. Working patients with MSDs visiting a physical therapy practice are the target group. The control group will receive normal physical therapy treatment. The intervention group will receive treatment from a physical therapist with more knowledge about work-related factors and skills in terms of integrating work participation into the patients’ care. Data are gathered at baseline (T0), at four months (T1) and eight months (T2) follow-up. Most outcomes will be assessed with validated patient-reported questionnaires. Primary outcomes are the limitations in specific work-related activities and pain during work. Secondary outcomes include limitations in general work-related activities, general pain, quality of life, presenteeism, sick leave (absenteeism), estimated risk for future work disability, work-related psychosocial risk factors, job performance, and work ability. Based on a sample size calculation we need to include 221 patients in each arm (442 in total). During data analysis, each outcome variable will be analysed independently at T1 and at T2 as a dependent variable using the study group as an independent variable. In addition to the quantitative evaluation, a process evaluation will be performed by interviewing physical therapists as well as patients.

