### Outcome assessment and data collection

All outcome measures will be self-reported measures. Data will be collected using online questionnaires filled in by the participating patients at the start of the intervention (T0), four months after the start of the intervention (T1, short-term effects) and eight months after the start of the intervention (T2, long-term effects). All questionnaires will be developed using Qualtrics online survey software (Qualtrics®). Outcome measures will be collected from the patients. The schedule for enrolment, outcome measures and time points is summarised in Table 1. Physical therapists will be asked to fill in a questionnaire at the start of the intervention and after eight months.

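### Two primary outcomes are each tested at four and eight months at p < 0.05 with no primary time point or success rule; if any one result can carry the claim, the false-positive risk is about 9% to 19%, against the single 5% used for the sample size.

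*Protocol article*

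**What the plan says.** The Abstract (Methods/design) states: "Primary outcomes are the limitations in specific work-related activities and pain during work". The Primary outcomes section describes the same two measures, both on 11-point scales.

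Outcome assessment and data collection sets the two follow-up times as "four months after the start of the intervention (T1, short-term effects) and eight months after the start of the intervention (T2, long-term effects"). They are labelled by duration only, and neither is called primary.

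Data analyses says "Each outcome variable will be analysed independently at T1 and at T2", with study group as the independent variable and adjustment for the baseline value of the outcome. The decision threshold is general: "Results will be considered significant if p < 0.05".

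The Sample size section opens with "The sample size was calculated based on the main outcome measures (11-item NPRS and 11-point PSFS") and proceeds "On the basis of two-sided testing, significance level of 0.05, power 0.8, accounting for the cluster design effect". It treats both outcomes together under one alpha and names no time point.

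**The concern.** Two outcomes at two times give four primary tests, each at the full 0.05. The protocol does not say whether the trial succeeds on one outcome or needs both, nor at which time. The sample size reads as if there were a single primary test.

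At stake is what a positive trial would mean. The hypothesis is broad, namely that the intervention improves the effectiveness of care, and the article foresees nationwide implementation once the trial is completed. With the rule as written, one nominally significant result out of four could be presented as confirming that hypothesis, with a false-positive risk well above the 5% used in planning. Once results are known, the choice of primary time point can no longer be made credibly.

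**Working it through.** **Inputs from the protocol.** Two primary outcomes (Abstract; Primary outcomes). Two follow-up times (Outcome assessment and data collection). Threshold 0.05 per test (Data analyses). Two-sided alpha 0.05, power 0.8, "an expected effect size of 0.7 and a standard deviation of 1.8", ICC 0.05, 15 clusters per arm of 10 patients, 10% extra clusters, 25% loss to follow-up (Sample size).

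**Inputs assumed.** Correlations between outcomes and between time points, and the correlation between baseline and follow-up. The protocol gives none of these, so ranges are shown.

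**Step 1: the plan's own figure.** Reading 0.7 as points on the 0 to 10 scale:
- Per arm without clustering: 2 × (1.8 × (1.960 + 0.842) / 0.7)² = 103.8.
- Design effect: 1 + (10 − 1) × 0.05 = 1.45. Then 103.8 × 1.45 = 150.5 per arm, or 15 clusters of 10.
- Extra clusters: 15 × 1.1 = 16.5, rounded up to 17.
- Loss to follow-up: 10 × 1.25 = 12.5, rounded up to 13 per cluster.
- Total: 17 × 13 = 221 per arm, 442 in all.

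The stated number reproduces with one undivided alpha of 0.05, so no allowance for several primary tests is built in.

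**Step 2: chance of at least one false positive among the four tests.**
- Independent tests: 1 − 0.95⁴ = 0.185.
- Correlated tests, by simulation of four normal test statistics (2,000,000 draws, two-sided). The first column gives all pairs the same correlation. The second gives outcomes and times that correlation each, and multiplies the two for pairs that differ in both.

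| Correlation | Equal for all pairs | Product structure |
|---|---|---|
| 0.5 | 15.5% | 16.1% |
| 0.7 | 13.0% | 13.7% |
| 0.8 | 11.4% | 12.0% |
| 0.9 | 9.4% | 9.8% |

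The range is therefore about 9% to 19%. Fixing one time point alone does not settle it: two outcomes at 0.05 each still give 1 − 0.95² = 9.75% if independent, and about 8% at a correlation of 0.8.

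**Step 3: power with Holm at one time point.** With 80% power at 0.05, the expected test statistic is 1.960 + 0.842 = 2.802. Holm rejects an outcome if it passes 0.025, or if it passes 0.05 and the other outcome has passed 0.025. By simulation, with a true effect of 0.7 on both outcomes and no baseline adjustment:

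| Correlation between outcomes | Per-outcome power | Power for at least one |
|---|---|---|
| 0 | 77% | 92% |
| 0.5 | 76% | 85% |
| 0.7 | 76% | 82% |
| 0.9 | 75% | 77% |

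A fixed 0.025 test (Bonferroni over two) would have Φ(2.802 − 2.241) = 71%. Holm does better because of its second step.

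Baseline adjustment divides the standard error by 1/√(1 − r²), where r is the baseline to follow-up correlation, taken here to act alike between and within practices. At r = 0.4 the expected statistic becomes 2.802 / √0.84 = 3.057, and Holm's per-outcome power is 83% to 85%.

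**Step 4: power if both outcomes must be significant at 0.05 at one time point.** Without baseline adjustment it is 0.8 × 0.8 = 64% if independent, 69% at a correlation of 0.5, 71% at 0.7 and 75% at 0.9. With adjustment at r = 0.5, the expected statistic is 2.802 / √0.75 = 3.235 and single-outcome power is Φ(3.235 − 1.960) = 90%. Power for both is then 81% (independent), 83% (0.5), 85% (0.7) and 87% (0.9).

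**The case against.** The strongest reply is that a journal article condenses the full protocol, that a statistical analysis plan may hold the multiplicity rule, and that the article points to a protocol in a public repository. That limits the finding, since the mere absence of an adjustment method would not count. It does not remove it. The article itself fixes separate tests at both times and an unqualified 0.05, and a later hierarchy would have to change that stated rule.

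A second reply is that no text says any single result counts as success. Short-term and long-term effects can be read as separate questions reported side by side, and whether to control error across them is debated for a trial of this kind. This stands as a condition: the inflated rate applies only if one positive result can carry the primary claim. The protocol neither states nor excludes that.

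Three stronger readings are tempting and not supported:
- A reader might take the false-claim rate to be at least 14%, whatever the circumstances. That needs the condition above and correlations no higher than about 0.7. Pain and limitation at work in the same patients may be more strongly correlated than that.
- A reader might infer that the plan fails either way, on alpha if one outcome suffices and on power if both are needed. The second half ignores the baseline adjustment that Data analyses already plans. With r = 0.5 the both-outcomes power is 81% to 87%.
- A reader might add further inflation by assuming that the linear regression ignores clustering. That is a separate question about the model and is not counted here.

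**Conclusion.** The concern holds in a conditional form. The article sets four primary tests at 0.05 each against a sample size built on one alpha of 0.05, and it leaves open which result supports the primary claim. If any one suffices, the chance of at least one false positive is about 9% to 19%, roughly two to four times the planned 5%. This rests on assumed correlations from 0 to 0.9 and on each test holding its own 5% level. Having two primary outcomes is legitimate, and the stated sample size reproduces. The defect is the missing decision rule. Because the repair is wording and needs no change to recruitment or data collection, this is a should-fix.

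**What to change.** Before any outcome data are seen, name either four or eight months as the primary time point. Test the two primary outcomes there with Holm's procedure at overall two-sided 0.05. Report the other time point and all secondary outcomes as supportive, with confidence intervals, and record the change in the trial register.

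The cost is a protocol and registry update plus some power: per-outcome power goes from 80% to about 75% to 77% before baseline adjustment, with about 77% to 92% for at least one outcome. The sample size does not credit the baseline adjustment already planned. At an assumed baseline to follow-up correlation of about 0.4 or more, that adjustment takes per-outcome power back above 80%.

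If the intent is that both outcomes must succeed at the primary time point, say so. No alpha split is then needed, but the power should be restated: about 64% to 75% without baseline adjustment, or about 81% to 87% with an assumed baseline correlation of 0.5.
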